## Abstract

**Background:**

Osteoradionecrosis of the mandible is the most common serious complication of radiotherapy for head and neck malignancy. For decades, hyperbaric oxygen has been employed in efforts to prevent those cases of osteoradionecrosis that are precipitated by dental extractions or implant placement. The evidence for using hyperbaric oxygen remains poor and current clinical practice varies greatly. We describe a protocol for a clinical trial to assess the benefit of hyperbaric oxygen in the prevention of osteoradionecrosis during surgery on the irradiated mandible.

**Methods/design:**

The HOPON trial is a phase III, randomised controlled, multi-centre trial. It employs an unblinded trial design, but the assessment of the primary endpoint, i.e. the diagnosis of osteoradionecrosis, is assessed on anonymised clinical photographs and radiographs by a blinded expert panel. Eligibility is through the need for a high-risk dental procedure in the mandible where at least 50-Gy radiotherapy has been received. Patients are randomised 1:1 to hyperbaric oxygen arm (Marx protocol) : control arm, but both groups receive antibiotics and chlorhexidine mouthwash. The primary endpoint is the presence of osteoradionecrosis at 6 months following surgery, but secondary endpoints include other time points, acute symptoms and pain, quality of life, and where implants are placed, their successful retention.

**Discussion:**

The protocol presented has evolved through feasibility stages and through analysis of interim data. The classification of osteoradionecrosis has undergone technical refinement to ensure that robust definitions are employed. The HOPON trial is the only multi-centre RCT conducted in this clinical setting despite decades of use of hyperbaric oxygen for the prevention of osteoradionecrosis.

**Trial registration:**

European Clinical Trials Database, ID: EudraCT200700622527. First registered on 5 November 2007.

**Electronic supplementary material:**

The online version of this article (doi:10.1186/s13063-017-2376-7) contains supplementary material, which is available to authorized users.

## Background

Osteoradionecrosis (ORN) describes the process where irradiated bone undergoes necrosis and becomes exposed through the investing soft tissues for a period of at least 3 months [1–3]. An important precipitating factor for mandibular ORN is surgical trauma, commonly dental extractions or implant placement following head and neck radiotherapy, but ORN can also occur spontaneously. ORN is painful and debilitating, often requiring surgical resection of the jaw and complex multidisciplinary management [4]. The morbidity and mortality of ORN is significant and treatment outcomes often unsatisfactory. Post-radiation extractions should, self-evidently, be performed atraumatically and antibiotics are commonly prescribed [5], but there is a paucity of high-quality evidence to guide best practice in the prevention of ORN.

Preventive approaches include pre-radiotherapy extraction of teeth and the use of hyperbaric oxygen (HBO) treatments or prophylactic antibiotics for post-radiotherapy extractions [6]. The overall incidence of ORN among post-radiotherapy patients is not certain but may have declined with improvement of radiotherapy techniques including intensity-modulated radiotherapy (IMRT) over recent decades [7]. However, the incidence of head and neck cancer, the proportion of cases receiving radiotherapy, and prognosis are all increasing [8], contributing to an expansion in the ‘at risk’ population where ORN prevention must be addressed. The risk of ORN with dental extractions is higher in the posterior mandible, with radiotherapy doses higher than 60 Gy (or with brachytherapy) and in smokers [9].

There have only been limited trials of prophylactic HBO. The single-centre randomised controlled trial (RCT) by Marx et al. [10] showed a significantly lower incidence of ORN after post-radiotherapy dental extractions in the HBO group when compared with the control group. There were two cases of ORN in 37 patients (5.4%) receiving HBO undergoing 156 extractions, compared with 11 cases in 37 patients (29.9%) undergoing 135 extractions receiving prophylactic penicillin, resulting in a number needed to treat (NNT) of 4. In a non-randomised retrospective study, Vudiniabola et al. [11] showed that of 29 patients who received pre-extraction HBO, 1 (3.4%) developed ORN; and of 7 patients who did not receive HBO, 1 (14.3%) developed ORN. Despite improvements in radiotherapy since the time of these studies, and evidence of a decreasing incidence of ORN [12], prophylactic HBO to prevent ORN has remained a standard of care for high-risk dental extractions [13].

HBO is not available to all patients as it requires proximity to a chamber, it is costly (approximately £4000–6000 per course) and sometime logistically problematic, requiring multiple daily visits. A typical protocol for prevention dictates 45 h of treatment over 30 compressions [10]. There are also risks associated with HBO therapy. A comprehensive recent safety review [14] noted common temporary visual problems, Eustachian tube problems 2%, claustrophobia 2% and seizure < 0.01.

A survey of UK practice revealed that, in a high-risk extraction of a lower mandibular molar, 33% ‘never’, 41% ‘sometimes’ and 26% ‘usually’ or ‘always’ prescribe prophylactic HBO [15]. Questionnaires of attitude to RCTs for HBO revealed that 93% of responders would wish to recruit such patients into multi-centre RCT [16]. Additionally, there is a lack of agreement on HBO protocol, with some UK patients referred for treatment in centres using non-standard pressures [17], lower than the typical 2.4 atmospheres (ATA) recommended in most ORN publications. Current National Institute for Health and Care Excellence (NICE) guidelines on the management of ORN recommend the use of HBO only as part of a clinical trial [18].

An additional question regarding the efficacy of HBO surrounds the placement of osseointegrated implants into the irradiated mandible, with the aim of preventing ORN or optimising bony healing and implant retention. Survey data again suggest wide disparity in practice [15] in the UK. No RCT has been carried out in this setting, and there are conflicting data from retrospective case control series [19, 20] as to whether HBO may enhance survival of implants in irradiated bone.

## Objective

The objective of the HOPON trial is to determine the benefit of HBO in the prevention of ORN subsequent to a surgical procedure in the ‘at risk’ irradiated mandible. The procedures included are high-risk dental extractions and the placement of implants. Additional outcomes are to document the incidence of ORN in the control group, the outcomes where ORN is diagnosed, and the retention of implants. The trial will also measure the effect of HBO in post-operative pain and effects on quality of life. The HOPON phase III trial protocol described here has evolved from the feasibility objectives in a preceding HOPON feasibility study.

## Methods/Design

### Design

HOPON is a prospective, multi-centre, randomised controlled, phase III trial to assess the effectiveness of preventing ORN after surgical procedures in the irradiated mandible. Although the patients and investigators are unblinded, the primary endpoint is assessed by a blinded panel for the presence and grade of ORN. Other endpoints are unblinded as they are recorded by either the patients or site investigators.

### Study population and eligibility

Patients who meet the eligibility criteria (Table 1) will be recruited either from routine review following the treatment of head and neck cancer, or following referral for oral rehabilitation. Detailed information on the benefits and risks of the study will be provided to the patients, including the provision of HBO at the nearest suitable trial chamber.

**Table 1 Tab1:** Eligibility criteria

Inclusion criteria	Exclusion criteria
Age > 18 years Prior radiotherapy to mandible > 50 Gy No evidence of cancer recurrence Condition requiring surgery to mandible: Extraction of premolar or molar Implant placement Provision of written informed consent in competent patient	Prior diagnosis of ORN of the mandible Prior HBO therapy for any indication Any previous prescription of systemic bisphosphonates, pentoxyphylline or tocopherol Pregnancy Contraindications to HBO: Lung disease (severe COPD or bullae) Middle ear Claustrophobia

*COPD* chronic obstructive pulmonary disease, *HBO* hyperbaric oxygen, *ORN* osteoradionecrosis

### Randomisation and blinding

Patients who meet eligibility criteria and have given informed consent will be randomly assigned by the Cancer Research UK Liverpool Cancer Trials Unit (LCTU). Randomisation will be in a 1:1 ration between HBO arm and control (non-HBO) arm, stratified by recruiting centre. The randomisation code list will be generated by the LCTU trial statistician by means of block randomisation [21] with randomly varying block length. The clinical team will be informed of the allocation of each patient by fax. Allocation of treatment is unblinded to local investigators and patients. The trial schema is shown in Fig. 1.

**Fig. 1 Fig1:**
[figure not shown]
Hyperbaric Oxygen for the Prevention of Osteoradionecrosis (HOPON) trial schema (Consolidated Standards of Reporting Trials (CONSORT) format)

### Trial intervention and control treatments

The supplier of the oxygen to be used will be dependent on standard practice within each hyperbaric unit. Treatment will be administered based around a version of the Royal Navy Therapeutic Table 66 – Repeat Hyperbaric Oxygen Therapy [22]. The patient undergoes pressurisation to 2.4 ATA at a tolerable rate. The patient undergoes decompression after 100% oxygen has been breathed at 2.4 ATA for a total of between 80 and 90 min. Air breaks while at 2.4 ATA may be introduced routinely or as required. The decompression is scheduled to control satisfactorily any risk to the patient and, if present, to the in-chamber attendant. Patients should breathe oxygen at an inspired partial pressure greater than 2.0 ATA for no more than 110 min during each individual treatment.

Patients in both arms of the trial are given chlorhexidine mouthwash and antibiotics. Pre- and post-operative chlorhexidine mouthwash 0.2% is used in a volume of 10 ml (i.e. one capful) washed around the mouth for around 1 min and spat out, three times daily (tds) for 5 days post-operatively. In case of chlorhexidine allergy, warm salt mouthwash at 1 teaspoon per cup of warm water is used. Orally administered antibiotics comprise amoxicillin 3 g 1 h pre-operatively (or 1 g administered intravenously) and 250 mg tds for 5 days post-operatively. In case of penicillin allergy this will be: 600 mg orally administered clindamycin (either 600-mg tablets orally (or the same dose of a 75-mg/5 ml suspension if tablets not tolerated) given 1 h pre-operatively (or 600 mg administered intravenously at the time of surgery) and 200 mg metronidazole orally tds for 5 days post-operatively.

### Outcome measures

The primary outcome measure is the diagnosis of ORN 6 months following surgery as determined by a blinded central review of clinical photographs and radiographs as well as the site investigator’s assessment. This blinded review is carried out by an expert panel, with access to paired clinical photographs and radiographs (orthopantomogram). Additionally, where possible, any area of exposed bone is presented in context of an in-field rule and/or site investigator’s measurement on the case report forms. The diagnosis of ORN at 3 and 12 months are secondary outcome measures, but determined in a similar way, the only difference being that radiographs will only be taken at these time points if ORN has been clinically diagnosed. A summary of the outcome measures and their time points is presented in Table 2.

**Table 2 Tab2:** Outcome measures, time of assessment and method of assessment

Outcome measure	Timing	Method of assessment
Primary outcome		
Presence of ORN	6 months	Blinded review of radiograph, clinical photograph with corroboration from site investigator’s assessment in CRF (and dimensions of any exposed bone)
Secondary outcomes		
Presence of ORN	3 and 12 months	As primary endpoint, but without radiographs unless ORN clinically evident
Severity of ORN	3, 6 and 12 months	Blinded review of radiograph, clinical photograph, site investigator’s assessment (and dimensions of any exposed bone) using modified Notani Score [23, 24]
Quality of life	3, 6 and 12 months	University of Washington head and neck cancer questionnaire
Pain following surgery	3, 6 and 12 months	Patient-reported on a Visual Analogue Scale and use of analgesia
Acute symptoms	Days 1 thru 7 post surgery	Patient-reported Likert scale for pain, swelling, trismus, normalcy of diet
Assessment of implants (where relevant)	At closure of trial	Casenote review, by loss of any implant placed as part of trial
Late follow-up of MBS cases (where relevant)	At closure of trial	Casenote review, by severity of ORN using modified Notani Score [23, 24].
Safety of HBO related to cancer recurrence	Within 12 months of trial treatments	SAE reporting.
Safety of HBO, otherwise	Within 28 days of HBO	AE/ SAE reporting of symptoms related to hyperbaric treatment

*AE* adverse event, *CRF* Case Record Form, *HBO* hyperbaric oxygen, *MBS* minor bone spicules, *ORN* osteoradionecrosis, *SAE* serious adverse event

The definition and classification of ORN used in the trial, based on that of Notani [23], has been subject to a technical refinement through protocol amendment following blinded analysis of the HOPON feasibility data [24], and is presented in Fig. 2. This was required to resolve inconsistencies which arose in cases where very small areas of exposed bone were seen: ‘minor bone spicules’ (MBS) were apparent, which occurred in 19% of patients in this initial analysis. In reporting cases with MBS, some trial investigators took a pragmatic position in judging MBS as clinically unimportant, likely gradually healing, and not reflecting progressive ORN. Others classified as Notani 1 ORN based on rigid definitions in common clinical use. When MBS was added as an additional distinct category to the classification (as < 20 mm^2^) this ambiguity was resolved and agreement between observers was achieved. This refinement was adopted by the protocol after discussion with trial oversight committees and the relevant regulatory bodies. A working assumption was made, after consultation, to group MBS with the healed (‘not ORN’) cases, but another outcome measure of the trial will be to test this assumption against the outcomes for later time points. For the purpose of the HOPON trial, radiological signs alone, or pain alone, are not considered ORN unless accompanied by a breach in overlying skin or mucosa.

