### Sensitivity analyses

These will consist of:Assessing the effects of assuming that:all pre-surgery dropouts would have developed ORNno pre-surgery dropouts would have developed ORNall pre-surgery dropouts would have developed ORN with risk for their armall pre-surgery dropouts would have developed ORN with mean risk across both armsAssessing the effect of adjustment in analysis of the primary outcome for radiotherapy dose, age, sex, tobacco and alcohol useInclusion of multiply imputed primary endpoint responses for all randomised patientsComparison of results using the site principal investigator’s (PI’s) original assessment of ORN (as with the primary analysis, this will include assessment of centre effects)Analysis of ‘blinded review’ ORN after including MBS vs excluding cases with only MBS

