The need for a blinded trial using sham treatments is considered desirable in trials where the primary endpoint is subjective or employ patient-reported outcome measures. In the HOPON trial the primary outcome is the presence of ORN, which is considered more objective, and additionally can be assessed on clinical photographs and radiographs at a remote time and location, by a panel of investigators who *are* blinded to the treatment arm received. However, the unblinded trial design for HOPON does introduce the possibility of reporting bias in some of the more subjective secondary outcomes such as quality of life or pain. Further, the unblinded design of the trial and need for extra treatments in the HBO arm introduces an inequality in time between randomisation and surgery for that arm. This potential methodological concern means that the time points commence at the time of surgery, rather than the date of randomisation, where it might be argued that only at randomisation are the two groups truly comparable.

Another difficulty that has arisen during the feasibility stage of the trial is the difficulty in robust allocation of some early stages of ORN. These have subsequently been classified as minor bone spicules (MBS), but are not reflected within any of the classifications of ORN currently in use. This difficulty is presumably not unique to the HOPON trial, yet it is difficult to ascertain from other similar studies how such cases have been dealt with. This is a problem created by taking a working ‘textbook definition’ of a clinical condition and extrapolating it as a primary outcome measure in a clinical trial. Because of the frequent (19%) finding of MBS during a blinded interim data review, it was logical to introduce an additional class to reflect this, the justification for which has been separately published [24]. To establish if any of the MBS cases in the HOPON trial will progress to clinically significant ORN, there is a secondary outcome measure of outcome of such patients at the conclusion of the trial. As a means to avoid any ambiguity, therefore, the use of the Notani classification with the additional category of MBS has been employed in order to avoid subjectivity and to enhance reliability and consistency of reporting.

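### The only outcome named for testing whether minor bone spicules belong with healed cases follows the spicule cases alone; the 12-month assessment, which also covers healed patients, should be assigned to that test

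*Protocol article*

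**What the plan says.** The Outcome measures section of the protocol article adds MBS, exposed bone under 20 mm², as a separate class and groups it with the healed cases for the primary endpoint. MBS was common in the feasibility data: "which occurred in 19% of patients in this initial analysis". The grouping is called a working assumption, and the section adds that "another outcome measure of the trial will be to test this assumption against the outcomes for later time points".

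Two places identify that measure.
- Table 2 has a row headed "Late follow-up of MBS cases (where relevant"), timed at closure of the trial. Its method is "Casenote review, by severity of ORN using modified Notani Score".
- The Discussion asks whether any MBS cases go on to clinically significant ORN, and answers that "there is a secondary outcome measure of outcome of such patients at the conclusion of the trial".

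Two other parts of the plan bear on the point.
- ORN is assessed in all patients at other visits: "The diagnosis of ORN at 3 and 12 months are secondary outcome measures, but determined in a similar way". Table 2 describes the method as "As primary endpoint, but without radiographs unless ORN clinically evident".
- The Sensitivity analyses section re-analyses the primary endpoint under different handling of MBS: "ORN after including MBS vs excluding cases with only MBS".

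**The concern.** To say that MBS belongs with the healed cases is to make a comparison: after 6 months, MBS patients should develop ORN about as often as healed patients do. The outcome named to test this has no healed group. The Background section says that ORN can also arise spontaneously, so some later ORN is possible in healed patients too, and a modest count among MBS cases has nothing to be set against.

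Two further features weaken the closure review as a test. "At closure" falls at a different interval after surgery for each patient, so early recruits have longer to progress than late ones. And it reads casenotes, whereas the classification it is meant to check comes from a blinded panel reading images.

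At stake is the support for the definition of the primary endpoint. The Outcome measures section reports that some investigators classed these same cases as Notani 1 ORN. If the MBS sensitivity analysis and the primary analysis disagree, readers will want to know which classification the later course of these patients supports.

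**Working it through.** **Inputs from the article**
- 103 evaluable patients per arm, so 206 in all (Sample size).
- ORN rate 5% in the hyperbaric oxygen arm and an absolute difference of 13.5 points, so 18.5% in control (Sample size).
- MBS in 19% of patients (Outcome measures).

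**The plan's own figure.** A two-proportion calculation for 5% against 18.5%, two-sided 5%, 80% power, with continuity correction gives 103 per arm. The odds ratio is (0.05/0.95)/(0.185/0.815) = 0.232. The stated sample size is reproduced, and this point does not affect it.

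**Expected group sizes at 6 months** (assuming that 19% holds in the full trial)
- MBS: 0.19 × 206 = 39.1, about 39.
- ORN: 0.05 × 103 + 0.185 × 103 = 5.2 + 19.1 = 24.2, about 24.
- Healed: 206 − 39 − 24 = 143.

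More patients depend on the grouping (39) than there are expected primary events (24).

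**What an MBS-only count can show** (exact two-sided 95% limits)

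| Progressions among 39 MBS | Risk | 95% CI |
|---|---|---|
| 0 | 0% | 0 to 9.0% |
| 2 | 5.1% | 0.6 to 17.3% |
| 4 | 10.3% | 2.9 to 24.2% |
| 8 | 20.5% | 9.3 to 36.5% |

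The first upper limit is 1 − 0.025^(1/39) = 0.090. Zero progressions would be reassuring in absolute terms, and eight would count against the grouping. Results in between are hard to read without a reference. If MBS is rarer, zero progressions say less: the upper limit is 16.1% with 21 cases (10% MBS) and 30.8% with 10 cases (5% MBS).

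**What the healed group adds.** The article gives no later ORN risk for healed patients, so the healed counts here are illustrative. Suppose 2 of 39 MBS cases have ORN at 12 months.
- With 3 of 143 healed (2.1%), the difference is 5.1 − 2.1 = 3.0 points.
- With 7 of 143 healed (4.9%), the difference is 5.1 − 4.9 = 0.2 points.

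The same MBS count is a possible excess in one case and none in the other. An MBS-only review cannot tell them apart.

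**How precise the comparison would be.** The 95% CI for the difference is Newcombe's. With Wilson limits (l, u) for each group, the lower limit is d − √[(p₁ − l₁)² + (u₂ − p₂)²] and the upper is d + √[(u₁ − p₁)² + (p₂ − l₂)²].
- 2/39 against 3/143: Wilson limits 1.4 to 16.9% and 0.7 to 6.0%; difference 3.0 points, CI −2.3 to 14.9.
- 8/39 against 3/143: Wilson limits 10.8 to 35.5% and 0.7 to 6.0%; difference 18.4 points, CI 7.9 to 33.5.

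Exact (Fisher) power, assuming a 12-month risk of 2% in healed patients:

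| True risk in MBS | 39 MBS, 143 healed | 21 MBS, 161 healed | 10 MBS, 172 healed |
|---|---|---|---|
| 5% | 15% | 10% | 8% |
| 10% | 53% | 35% | 24% |
| 15% | 82% | 61% | 42% |
| 20% | 95% | 80% | 58% |

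The comparison would detect a large excess but not a small one.

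**The case against.** A reader might infer that the trial has no later data on healed patients and so cannot support or refute the grouping at all. The documents do not support that. ORN presence and severity at 12 months are outcomes for all patients, with no restriction to MBS cases, so a healed comparator exists after the 6-month endpoint. An MBS-only count also carries information on absolute progression, as the first table shows. And the MBS sensitivity analysis already checks whether the primary result depends on the grouping, although it does not check whether the grouping is right.

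Three more arguments deserve an answer.
- The article speaks of later time points in the plural, which could include 12 months. It could, but the same sentence calls the test another outcome measure, and Table 2 and the Discussion describe one outcome for this purpose: the closure review.
- The Discussion frames the question as whether any MBS cases progress, which needs no comparator. That is fair for that question. The assumption stated in Outcome measures, that MBS sits with healed, is wider.
- Which patients are tabulated against which is usually left to the analysis plan, which is not shown and may cover this. That stands as a reason for restraint. But the article itself sets the population, timing and method of the closure outcome, and that specification can be assessed as written.

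It is also true that a comparator does not cure the small number of MBS cases: power is only 15% if the true risks are 5% and 2%.

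**Conclusion.** The point holds in a limited form. The one outcome the article ties to the MBS assumption is uncontrolled, varies in length of follow-up and uses a different method from the panel read. It can describe absolute progression but not excess risk over healed patients. The data for a better test are already planned; what is missing is their assignment to it.

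This does not make the primary endpoint invalid, and it does not affect the sample size or the primary analysis. The sizes given (39 MBS, 143 healed) assume that the feasibility MBS rate persists, that the planning ORN rates hold and that all these patients are seen at 12 months. The power figures also assume a 2% risk in healed patients, which is not in the article. It is an inexpensive improvement that is worth making.

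**What to change.** In the Outcome measures text and Table 2, state that the MBS assumption will be tested by comparing patients classed as MBS at 6 months with those classed as healed at 6 months, on the reviewed ORN diagnosis at 12 months. Report the risk in each group and the difference with a 95% CI, overall and by arm. Since 6-month status arises after randomisation, the by-arm figures are descriptive.

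Say explicitly that the 12-month diagnosis used is the blinded review. The Design section says endpoints other than the primary are unblinded, whereas Outcome measures says the 12-month diagnosis is determined in a similar way to the primary.

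Keep the closure casenote review of MBS cases as supportive. Keep the MBS sensitivity analysis as the check on whether the primary result depends on the grouping.

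The cost is a wording change and one extra tabulation of data already planned. With groups of this size, present the result as an estimate with its interval; a non-significant difference must not be read as showing that MBS and healed cases are equivalent.
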